## Methods/Design

### Objectives of the study

The overall goal of the project is to evaluate the feasibility and impact of the FICare model in a multicenter cluster randomized controlled trial in six NICUs in China.

The objectives of the pilot study are:To obtain information about what parents think will be the most difficult challenges to overcome in the study, and what doctors and nurses think will be the most difficult challenges to overcome in the study to aid in developing the program procedures, parent education material, and staff training material.To recruit a medical staff member at each site to participate in leading the implementation of the main study at their site and train staff in educating parents and enabling them to participate in NICU care.To get data from at least 90 infants and their parents (45 from the intervention site and 45 from the control site) to confirm or adjust the sample size calculation.To assess the feasibility of the proposed procedures to help parents participate in taking care of their preterm but medically stable infants in the NICU, as measured by percentage enrollment in the pilot study, number of education sessions provided and parent attendance, amount of time parents spend in NICU, feedback from parents, and nursing staff.

### Hypotheses

The primary hypothesis is that the implementation of the FICare model for preterm infants in Chinese NICUs will result in a significant reduction in nosocomial infection and hence length of hospitalization. The secondary hypotheses are: (1) implementation of the FICare model in Chinese NICUs will improve maternal and infant outcomes including infant weight gain, maternal stress, and breastfeeding rates; (2) implementation of the FICare model in Chinese NICUs will result in decreased total medical expenses for preterm infants.

### Setting and sample

In this multicenter cluster randomized control trial, six tertiary-level NICUs in three different cities (two NICUs in each city) will be randomized to two groups: FICare or control groups, such that the three NICUs in each group are from different cities. A total of 588 eligible infants (294 in each group, and 98 in each NICU) for whom parental consent has been obtained will be enrolled (the enrollment rate will be approximately 11 to 18 %). An internal pilot study will be first conducted in two NICUs, one from the FICare group and one from the control group. In all, 90 infants (45 from each NICU) will be recruited for the pilot study. The recruitment period of the pilot study will take around 10 months. It is estimated that 540 to 640 eligible infants (the estimated enrollment rate is approximately 21 to 25 %) are admitted to attending NICUs each year.

Patient inclusion criteria are:Infants are born at a gestational age of more than 28 weeks but less than 35 weeks;Infants have been receiving enteral feeds for more than 24 h; andInfants have vital signs that have been stable for more than 24 h. Patients must meet all three criteria.

Patient exclusion criteria are:Infant requires either invasive or non-invasive ventilation support;Infant requires surgical intervention;Infant is receiving palliative care;Parents have severe social issues or there is a language barrier;Infant is likely to be discharged within 1 week;Care-provider is not willing to commit to staying in the hospital for more than 6 h per day;Parents refuse to give consent; orInfant weighs less than 400 g at birth.

Patients, parents or care-givers meeting any one of these criteria should be excluded.

Patient discharge criteria are:Daily enteral feed is more than 160 ml/(kg day) and infants tolerate enteral feeding well;The infant has regained birth weight plus the body weight is more than 2 kg;Vital signs are stable;Neither intravenous medication nor oxygenation is needed;The baby gains weight for at least three consecutive days; andA car-seat test is passed if the parents drive.

Patients must meet all six criteria before being discharged home.

### Baseline assessments of joining neonatal intensive care units

Before inviting NICUs to join this study, a baseline assessment of candidate NICUs was completed. The baseline assessment was based on space size, number of beds, number of nurses and physicians, nurse-to-bed ratio, nurse-to-physician ratio, number of preterm infants admitted per year, and average total hospital stay of preterm infants. There must be no significant difference between joining NICUs. Finally, six tertiary NICUs were invited to join this study.

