**Fig. 1 Fig1:**
[figure not shown]
Flow chart of study design. This is a cluster randomized control trial about family integrated care (FICare) in China. This 3-year research is divided into two stages: an internal pilot study (1 year) and a main study (2 years). Ethical approval will be obtained first, followed by recruitment of research collaborator. After basement data collection, six level III NICUs in different tertiary hospitals will be randomly divided into two groups: the FICare group and the control group. Questionnaires about the demands of and attitude to FICare, and recruitment lectures about FICare will be completed in the early stage of the internal pilot study. A small number of patients will be enrolled in the internal pilot study. The data in the internal pilot study will be used to re-adjust the final sample size. Primary outcome measure data and secondary outcome measure data will be collected in both the internal pilot study and the main study. Data will be statistically analyzed at the end of the whole study

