### Data analysis

Data analysis will be conducted on an intention-to-treat basis. To take into account the clustering effect, Student’s *t* test adjusted for the inflation factor (or design effect) [11, 12] will be used, to compare the primary outcome between the FICare and control groups. Furthermore, a two-level hierarchical linear regression model will be used to compare the primary outcome measure between the two groups, accounting for patient-level characteristics, such as gestational age, small for gestational age, sex, Apgar score at 5 min, maternal age, delivery mode, maternal hypertension, chorioamnionitis, maternal education, and the NICU-level covariates (NICU size, number of nurses, and neonatologists). To take into account the cluster effect, a symmetric covariance matrix structure will be used for the models.

The secondary outcome measures will also be compared between the two groups using Student’s *t* test for continuous variables and the chi-square test for categorical variables adjusted for the inflation factor. A two-level hierarchical linear regression model or a logistic regression model, as appropriate, will be applied for the comparison of the outcomes between two groups, accounting for patient-level and NICU-level characteristics.

To assess the rate of growth for the two groups, we will further examine the rate of weight change over time, if applicable. Linear or nonlinear mixed-effect models for longitudinal data will be used to compare the rate of change in weight gain between the two groups, adjusted for duration of hospital stay, and patient-level and NICU-level characteristics. An interim analysis for the internal pilot study will first be conducted using similar methods, if applicable. The preliminary results will then be used to re-justify the sample size, using the method of Lake et al. [10].

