China is a large country with 30 provinces, each with varying economic status, a factor that may have a significant influence on the outcomes of infants in the NICU. In addition, we do not want to conduct this study in a NICU with too many beds, as it may be difficult to maintain the quality of the study in a larger NICU, particularly in terms of problems with human resources, such as varying availability of nurses or inconsistent shift patterns. Our main objective during our baseline research was to collect data on Chinese NICUs, including the number of NICU beds, mean birth weight of patients, percentage of preterm babies, percentage of babies with gestational age <32 weeks, nurse–patient ratio, mean hospitalization period, total medical expense per patient, top three reasons for early discharge home, re-admission rate within 30 days after discharge, and possibility of allowing parents to enter NICU (0 = impossible, 1 = probable, 2 = very possible, 3 = already allowed). As a result of our analysis we identified and recruited six NICUs at the same academic level from three provinces, all from cities with an above-average economic level. The NICUs are all similar in size and have a similar patient mix. Thus, we have tried to ensure that program implementation will be as consistent as possible across the six sites with fewer barriers linked to economic status and availability of hospital and parent resources. Following success in this study we will be able to expand the program to examine whether it is feasible in regions with a lower economic status and more financial challenges.

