We estimate that there will be a drop-out rate of approximately 10 % of families who enroll in the study, mostly owing to financial issues or time constraints. To minimize the effect of the biases this could introduce, we will conduct analysis with an intention-to-treat basis. There are limitations to this study. Unlike a randomized controlled trial, where patients are randomized rather than centers, some potential confounders, such as sex, gestational age, or birth weight, cannot be complete controlled for. To minimize the biases that may exist between two centers because of this, we will use multilevel models to compare the outcomes between two groups adjusting for these potential confounders in the analysis stage. We will also adjust the analysis for any potential confounders due to differences in the NICUs (NICU size, number of nurses, and neonatologists). Since the eligible infants in a NICU cannot be identified before randomization, i.e., consent cannot be obtained before randomization, this could introduce a selection bias. To minimize this bias, we will ensure that the recruitment of infants is conducted by a research coordinator who is blind to group allocation.

The project proposed here will take the principles of the FICare model as described by the Mount Sinai Hospital group and see how they can be applied to Chinese NICUs and what the outcomes are. The key pillars of this project are [8]:Mothers or close family members are present in the NICU to take care of their newborn infants and collaborate with the NICU medical team in the infant’s care;Parent education is provided, such that parents can truly participate;Infant holding and parents being present at their infant’s bedside is supported by unit policies, physical, and environmental supports;Nurses are provided with tools and education to enable families to be part of the care team; andThe entire care team supports the model of care.

The project is a multicenter cluster randomized controlled trial and is not a technology-based project. The approach used in this project could be transferable to many other areas of medical care, such as pediatrics, chronic care, and geriatrics. Data in this project can be used to inform health policy in NICUs across China so that parents can be allowed to enter the NICU and be at their infant’s bedsides during baby’s hospitalization, and modifying the design of NICUs in China to facilitate the participation of parents in caring for their newborn infants.

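### The hierarchical model spends three NICU-level covariates on six NICUs, leaving 1 degree of freedom, and omits the pre-randomisation NICU measure closest to the primary outcome: baseline hospital stay

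*Protocol article*

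**What the plan says.** **Baseline data.** The section on baseline assessment of the NICUs lists what was compared before units were invited. The list ends with "number of preterm infants admitted per year, and average total hospital stay of preterm infants". The Discussion describes the same exercise and again includes "nurse–patient ratio, mean hospitalization period, total medical expense per patient".

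**Timing.** The Fig. 1 legend places this before allocation: "After basement data collection, six level III NICUs in different tertiary hospitals will be randomly divided into two groups".

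**Stated use.** The baseline section says "There must be no significant difference between joining NICUs". It gives no test, margin or observed values. The Randomization section describes a drawing of lots that does not use baseline stay.

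**Analysis.** Data analysis specifies a t test adjusted for the design effect, and a two-level hierarchical model with patient-level characteristics "and the NICU-level covariates (NICU size, number of nurses, and neonatologists". The Discussion repeats the same three as adjustment for "any potential confounders due to differences in the NICUs (NICU size, number of nurses, and neonatologists". The patient-level list is introduced as examples. The NICU-level list is closed and appears twice, so it reads as a stated choice and not as condensed text.

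**The concern.** The randomised units are six NICUs, three per arm. An arm comparison that respects this has at most 4 between-NICU degrees of freedom, and each NICU-level covariate removes one. The plan spends three of the four on indirect descriptors of the unit. It leaves out the one NICU-level quantity it holds from before allocation that measures the primary outcome itself, although in preterm infants generally.

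The screen does not justify the omission. A non-significant difference is not evidence of equality. The plan does not treat the screen as sufficient either: beds and staffing were screened in the same way, and size and staffing are still adjusted for.

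At stake is whether the adjusted comparison can be informative at all, and whether a reader can see how alike the arms were at the start.

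**Working it through.** **Inputs from the protocol article.** Sample size calculation: SD 15 days, target difference 5 days, ICC 0.01, 10% drop-out, 293 per group, 98 per hospital. Setting and sample: six NICUs, three per arm, and 540 to 640 eligible infants a year.

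**Assumptions.** Two-sided alpha 0.05; 88 evaluable infants per NICU (98 × 0.9); about 300 infants behind each baseline mean; arm difference judged on between-NICU degrees of freedom; city pairing ignored. r is the correlation between a NICU's true baseline and true trial-period effect. The documents give no value for it.

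**1. The plan's own figure.** Unclustered n per group = 2 × [15 × (1.960 + 0.842)/5]² = 141.3. Design effect = 1 + 87 × 0.01 = 1.87. Then 141.3 × 1.87 = 264.2, and 264.2/0.9 = 293.5, against 293 stated. It reproduces.

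**2. What the screen lets through.** The largest non-significant difference between two NICUs with k infants each is 1.96 × 15 × √(2/k). The yearly figure does not say how many NICUs it covers, so both readings are shown, using eligible infants as a stand-in for the infants behind the baseline means.

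| Reading of 540–640 a year | k per NICU | Largest non-significant difference |
|---|---|---|
| Two NICUs | 270 to 320 | 2.5 to 2.3 days |
| Six NICUs | 90 to 107 | 4.4 to 4.0 days |

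**3. Arm-level imbalance.** Between-NICU SD = 15 × √0.01 = 1.5 days. SD of the three-versus-three difference = 1.5 × √(2/3) = 1.22 days; 95% limit = 1.96 × 1.22 = 2.4 days. The chance of more than 2 days is 10%, and of more than 4 days 0.1%. At ICC 0.03 the 95% limit is 4.2 days.

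**4. Degrees of freedom.**

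| NICU-level terms besides intercept and arm | df | Critical t |
|---|---|---|
| None, or change from baseline | 4 | 2.78 |
| Baseline stay only | 3 | 3.18 |
| Size, nurses, neonatologists (as stated) | 1 | 12.71 |
| Those three plus baseline stay | 0 | not estimable |

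Baseline stay therefore cannot be added to the list; it has to replace it.

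**5. Expected 95% half-widths, ICC 0.01.**
- No NICU covariate: 2.78 × √[2 × (2.25 + 225 × 0.99/88)/3] = 2.78 × 1.785 = 4.96 days.
- Stated three covariates, on the generous assumption that they remove all true between-NICU variation and that their slopes cost nothing: 12.71 × √(2 × 2.531/3) = 12.71 × 1.299 = 16.5 days.

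**6. Simulation of the six-NICU regression, r = 0.8.** The three covariates were simulated as unrelated to outcome.

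| Analysis | ICC 0.01 | ICC 0.05 |
|---|---|---|
| No NICU covariate, mean half-width | 4.7 days | 7.9 days |
| Baseline-stay covariate, mean half-width | 5.4 days | 7.4 days |
| Baseline-stay covariate, median | 5.0 days | 6.9 days |
| Stated three covariates, median | 27 days | 45 to 46 days |

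Medians are used for the last row because with 1 df the half-width is very skewed. At ICC 0.01 and r = 0 the baseline-stay median is 5.7 days, still far below 27.

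**7. Change from baseline.** Variance per NICU = 2 × 225 × ICC × (1 − r) + 225 × (1 − ICC)/88 + 225/300. At r = 0.8 the half-width on 4 df is 4.64 days at ICC 0.01 (against 4.96 unadjusted) and 6.28 at ICC 0.05 (against 8.38). Setting this variance equal to the unadjusted one gives a break-even r = 0.5 + 1/(600 × ICC): 0.67 at ICC 0.01 and 0.53 at ICC 0.05.

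**The case against.** **Randomisation and the clustered analysis already deal with site differences.** This largely stands. NICUs are allocated by lot, the t test carries a design effect and the model has two levels, so chance site variation enters the standard error. A reader might infer that pre-existing differences of 2 to 4 days will be taken for a FICare effect. The documents do not support that: 2.3 to 4.4 days is a screening limit for pairs of single NICUs, the arm-level figure is smaller, and no observed difference is reported.

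**The units were made alike.** Similar NICUs were chosen, the three in each arm come from different cities, and six common discharge criteria apply. These reduce site variation but do not remove it. Stay is counted from admission, so it includes time before enrolment. The Discussion itself accepts that NICU differences need adjustment.

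**Baseline stay may not help.** This also stands, measured against the unadjusted comparison. The collected mean covers preterm infants generally, not stable infants in the trial's gestational range who are expected to stay beyond a week. At ICC 0.01 the covariate does not repay its degree of freedom even at r = 0.8.

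**Covariate choice belongs in an analysis plan that is not shown.** That would answer a silence. Here the article fixes a closed list and repeats it.

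**Conclusion.** The point holds as a cheap improvement to the stated model. Three NICU-level covariates on six NICUs leave 1 df, which makes the adjusted comparison close to uninformative: a 16.5-day half-width even on generous assumptions, against a 5-day target. Using baseline stay instead leaves 3 df and is better than the stated model at every r and ICC tried. That conclusion assumes that inference uses between-NICU degrees of freedom. A model using infant-level degrees of freedom would look more precise but would rest on an understated uncertainty.

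Two stronger readings should be resisted. This is not systematic bias: at the planned ICC it is a chance arm imbalance of about 1.2 to 2.4 days, plus lost precision. Nor does baseline adjustment reliably improve on the comparison without NICU covariates: that depends on r and the ICC, and r is unknown.

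**What to change.** - In Data analysis, and in the matching sentence of the Discussion, replace NICU size, number of nurses and number of neonatologists with the NICU's baseline mean hospital stay as the only NICU-level covariate.
- Keep the comparison without NICU-level covariates alongside it.
- Report the arm difference in NICU-level change from baseline stay (4 df) as a supporting result.
- In the baseline assessment section, replace the reliance on non-significance with the six baseline values shown by arm.

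**Cost.** A change of model wording and one small table. The covariate takes one between-NICU degree of freedom, against three now; change from baseline takes none. The general preterm mean is already held. Restricting it to the trial's gestational range would be preferable but may need re-extraction, because the documents do not show that such a mean exists. The table is useful whatever r turns out to be.

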### Randomization

Since the intervention could not be completely blinded in this study, we choose a cluster randomized controlled trial design in which hospitals are randomized into two groups (intervention and control groups) instead of patients, to avoid contamination of patients in control groups. Since only six are NICUs participating in this study, the randomization was completed by a method of drawing lots by two third-party persons who are blinded to this project. In detail, the name of each participating hospital was written a piece of paper and put into an envelope by a person who was not aware of this project. The six envelopes were identical. Another person who was also blinded to this project randomly divided the six envelopes into two groups (the intervention group and the control group), with three NICUs in each group.

### Sample size calculation

The proposed sample size is based on the primary outcome of duration of hospital stay. From our previous clinical data and similar clinical research reports from our Canadian colleagues [9], the average duration of hospital stay is 28 days with a standard deviation of 15 days. We expect a decrease in hospital stay of 5 days (an approximate 18 % decrease) in the FICare group compared with the control group. Based on this expectation, the sample size was estimated using the method of Lake et al. [10], assuming an intra-cluster correlation coefficient of 0.01. We estimate that a total sample size of 586 (293 for each group or 98 for each hospital) will achieve a power of 80 % to detect the expected 18 % decrease in duration of hospital stay in the FICare group compared with the control group, taking into account a 10 % drop-out rate following enrollment in the study. This sample size will be re-adjusted in the interim analysis at the completion of the pilot study.

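### The stated 80 % power makes no allowance for only six randomised NICUs; on the 4 degrees of freedom available, power for the 5-day effect is about 56–59 %.

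*Protocol article*

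**What the plan says.** The Sample size calculation section of the Protocol article gives these inputs:

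- Mean and SD: "the average duration of hospital stay is 28 days with a standard deviation of 15 days".
- Effect: "We expect a decrease in hospital stay of 5 days (an approximate 18 % decrease) in the FICare group".
- Clustering: "assuming an intra-cluster correlation coefficient of 0.01". No source or range is given for this value.
- Result: "a total sample size of 586 (293 for each group or 98 for each hospital) will achieve a power of" 80 %, "taking into account a 10 % drop-out rate following enrollment in the study".

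The Setting and sample section rounds the total to 588 (294 per group, 98 per NICU). Alpha and sidedness are not stated.

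The Randomization section makes the NICU the unit of allocation: a third party "randomly divided the six envelopes into two groups (the intervention group and the control group), with three NICUs in each group". The Data analysis section plans a t test corrected by the design effect, without giving its degrees of freedom. It adds a two-level model with three NICU-level covariates. The sample size is to be revisited after the internal pilot by the same cited method.

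The section on baseline assessment of the NICUs lists "average total hospital stay of preterm infants" among the data already collected from candidate units.

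**The concern.** A design effect inflates the variance for clustering, but it does not allow for how poorly that variance is known when there are very few clusters. With six NICUs, the between-NICU component is estimated from six means, and the reference distribution has to reflect this. A calculation that uses 1.96 and 0.84 is close to right with many clusters and seriously optimistic with three per arm.

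The stakes lie in how the result is read. The article says the data may inform NICU policy across China. If readers believe the trial had 80 % power, they will take a non-significant result as evidence against FICare. In fact a true 5-day reduction would be missed in roughly 41–44 % of such trials, even if the ICC really is 0.01.

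**Working it through.** **Inputs.** From Sample size calculation: difference 5 days, SD 15 days, ICC 0.01, power 80 %, drop-out 10 %. From Randomization: three NICUs per arm. Assumed: two-sided alpha 0.05.

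**Step 1: reproduce the plan's figure.**

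- Individually randomised size per arm: 2 × (1.960 + 0.8416)² × 15² / 5² = 141.3.
- With n evaluable per arm in three NICUs, the design effect is 1 + (n/3 − 1) × 0.01. Solving n = 141.3 × [1 + (n/3 − 1) × 0.01] gives n = 264.4, about 88 per NICU, with design effect 1.87.
- Allowing for drop-out: 264.4 / 0.9 = 293.7 per arm, 587.5 in total. The plan states 293 and 586.

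The plan's number is therefore reproduced with normal quantiles. A t distribution with infant-level degrees of freedom (about 527) gives 79.9 % power, so it leads to the same place. Neither allows for the small number of clusters.

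**Step 2: same inputs, 4 degrees of freedom.** Six cluster means less two arm means leave 4 df, and the two-sided 5 % critical value is 2.776. The noncentrality is 5 / SE, with SE = √(2 × 225 × DE / n).

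- 88 evaluable per NICU (n = 264, DE = 1.87): SE = 1.785, noncentrality 2.80. Normal power 80.0 %; noncentral t power **56.4 %**.
- 98 per NICU, no drop-out (n = 294, DE = 1.97): SE = 1.736, noncentrality 2.88. Normal power 82.1 %; noncentral t power **58.6 %**.

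Simulating a t test on the six NICU means (200,000 trials each) gave 56.6 % and 58.7 %.

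**Step 3: what the design can detect.** For 80 % power on 4 df the noncentrality must be 3.76. The detectable difference is 3.76 × 1.785 = 6.7 days after drop-out, or 3.76 × 1.736 = 6.5 days without it. To detect 5 days with three NICUs per arm would take about 555 evaluable infants per NICU, or 3 × 555.5 ≈ 1,670 per arm. Adding infants is therefore not a practical remedy.

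**Step 4: dependence on the ICC.** The between-NICU SD implied by an ICC is √(ICC × 225). The values other than 0.01 are illustrative, because the document gives no range.

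| ICC | Between-NICU SD (days) | Power on 4 df, 88 to 98 per NICU |
|---|---|---|
| 0.005 | 1.06 | 67–70 % |
| 0.01 | 1.50 | 56–59 % |
| 0.02 | 2.12 | 42–44 % |
| 0.05 | 3.35 | 25 % |

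**Step 5: can the internal pilot correct this?** The pilot uses two NICUs, one per arm, so the difference between NICUs cannot be separated from the effect of treatment. The re-estimation uses the same method, and the document makes no provision for adding NICUs.

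**The case against.** The strongest reply is that power belongs to a test, and the Data analysis section names one: a t test corrected by the design effect, with no degrees of freedom given. If it is run with infant-level degrees of freedom and the ICC fixed at 0.01, 80 % is the matching power. That is true, but the test is then valid only if the ICC is no higher than 0.01. With 0.01 plugged in and a true ICC of 0.02, the two-sided type I error at 88 per NICU is 2 × [1 − Φ(1.96 × √(1.87/2.74))], about 10.5 %. At a true ICC of 0.05 (design effect 5.35) it is about 25 %.

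Other objections, and what remains of them:

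- *The use of normal quantiles is inferred.* This is correct: the article cites a method and does not show the formula. Infant-level t quantiles would serve equally well, and the missing allowance for six clusters is the same either way.
- *Alpha is unstated, and one-sided 0.05 would be kinder.* It gives about 74–76 % on 4 df, still below 80 %. It would also have led to about 195 infants per arm, not 293.
- *The 4 df is not settled.* Setting and sample describes one NICU per arm in each city, while Randomization describes an unrestricted draw. A city-paired analysis would leave 2 df and, at the same variance, about 35–37 % power. The three NICU-level covariates in the second model also use up degrees of freedom. These points lower the figure.
- *Patient-level covariates could recover some precision.* They could, but the sample size section claims no such gain.
- *The NICUs were chosen to be alike, and an article may leave the source of the ICC to a fuller document.* Both points are fair, so the missing source is secondary. The main finding uses the plan's own ICC.

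**Conclusion.** The concern holds. On the plan's own difference, SD, ICC and drop-out, the design has 56–59 % power for 5 days, not 80 %, and reaches 80 % only at about 6.5–6.7 days. This rests on a two-sided 0.05 test, a between-NICU variance estimated from the six NICUs on 4 df, and no precision gained from covariates. It is the favourable end at ICC 0.01 if city pairing or NICU-level covariates enter the analysis. A larger ICC lowers it sharply. The sample size itself is arithmetically consistent with a large-cluster formula; the power claimed for it is wrong for a six-NICU trial.

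**What to change.** In Sample size calculation, replace the 80 % statement with wording such as: *With three NICUs per group and a two-sided 5 % t test on 4 degrees of freedom, 588 infants give about 57 % power for a 5-day difference (80 % for about 6.6 days) at an ICC of 0.01.* Then:

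- Give the power at ICC 0.005, 0.02 and 0.05 alongside it.
- Compare the 1.5-day between-NICU SD implied by ICC 0.01 with the spread of the six NICUs' baseline average stays. Those averages cover preterm infants generally and carry their own sampling error, so the check is approximate, but the data are already in hand.
- State the same reference distribution in Data analysis, so that the power and the planned test refer to one another. If a city-paired analysis is intended, quote its power instead.

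The cost is rewording and a less favourable published power. No extra infants are needed.
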